## 5. STUDY END POINTS

### 5.1 Primary End Point(s)

#### **Safety:**

- Determine AEs and SAEs associated with NO-impregnated catheters
- Proportion of patients (%) who prematurely discontinued the study due to AEs or SAEs

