#### **Tolerability:**

- Proportion of patients (%) who prematurely discontinued the study due to AEs or SAEs associated with NO-impregnated catheter

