#### 7.5.1 Criteria for Treatment Discontinuation

- AEs that are suspected to be related to NO-impregnated catheters, according to physician discretion

- Blood pressure and heart rate above or below the 20% of the normal ranges for the patient baseline

A patient whose treatment was discontinued for any reason should complete all study assessment including the follow up visits.

Concomitant medication (i.e. antibiotics) given during the study will not be a reason for treatment early discontinuation.

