### **7.5.2 Criteria for Early Study Withdrawal**

A patient may withdraw or be withdrawn from the study for the following reasons:

- 1) Patient withdrew consent.
- 2) Protocol violation/ non-compliance.
- 3) Loss to follow-up/failure to return.
- 4) Patient with difficulty in insertion of catheter during surgery.
- 5) In cases which require catheter replacement.
- 6) Serious adverse event

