## 8.6 Termination/Study Early Discontinuation

Treatment/study can be either temporarily or permanently discontinued. Criteria for discontinuation are specified in section 7.5

The reason for discontinuation of study will be documented in the source documents and captured on the CRF. In the event that the catheter is removed prematurely, end of treatment assessments (section 7.4) should be completed as close to the last date as possible.

If a patient is withdrawn because of an AE, the appropriate "Withdrawal Section" of the CRFs should be fully completed in addition to the AE module. ENOX BIOPHARMA should be informed of all patients who are withdrawn for this reason.

Documented attempts will be made to follow a patient who prematurely discontinues the study.

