## **16. DATA HANDLING**

### **16.1 Data Collection via Paper CRF**

CRFs for individual patients will be provided by the sponsor. The CRFs are supplied on NCR paper; one copy will be kept by the investigator and the original and second copy will be retrieved by the ENOX study monitor.

CRFs are used to record study data and are an integral part of the study and subsequent reports. The data requested on the CRF must be recorded in black/blue ink (hard point pen) as the study is in progress. Additional information may be included as warranted. Any correction or deletion should be made by drawing a single line through the entry so that the original entry is still legible; this change must be initialed and dated by study staff personnel. Changes regarding AEs and clinical judgments must be initialed and dated by the investigator.

CRFs will be considered complete when all missing and/or incorrect data have been accounted for. Copies of the study records must be retained in the files of the investigator in accordance local regulations.

Completed CRFs must be signed by the investigator for each patient enrolled, including those prematurely terminated from the study for any reason. The reason for premature termination must be recorded by the investigator for each patient, on the termination visit CRF page.

CRFs must be kept current to reflect the patient's status at each phase during the course of the study. Patients should not be identified by name; appropriately coded identification and patient's non-identifiable initials must be used. The Investigator must keep a separate log of the patients' names, used initials and addresses and it must be maintained confidential.

CRFs must be completed and available for on-site review at each monitoring visit and within 14 working days of a patient's termination from the study.

All source documents, such as clinic charts, must be available to allow source data verification.

CRFs will be sent to the DMC (Data Management Center- Medistat) promptly after the visit has been monitored.

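### The study-withdrawal reasons in 7.5.2 are narrower than the primary discontinuation endpoints, and 7.5.1 keeps patients in the study after a catheter stop, so cases driven by non-serious AEs may be missed

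*Protocol*

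**What the plan says.** **Endpoints.** Protocol 5.1 makes two discontinuation proportions primary. The safety one is "Proportion of patients (%) who prematurely discontinued the study due to AEs or SAEs". The tolerability one counts patients who "prematurely discontinued the study due to AEs or SAEs associated with NO-impregnated catheter". Section 13 (Safety and Tolerability) plans a 95% confidence interval for discontinuation due to any AE or SAE, and 13.4 (Tolerability Assessments) reports failure to complete because of AEs. None of these is limited to serious events.

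**Study withdrawal.** 7.5.2 opens with "A patient may withdraw or be withdrawn from the study for the following reasons" and lists six: consent withdrawn, protocol violation or non-compliance, loss to follow-up or failure to return, difficult insertion, catheter replacement, and "6) Serious adverse event". There is no open-ended item, and nothing says what to do when several reasons apply.

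**Treatment discontinuation.** 7.5.1 lists "AEs that are suspected to be related to NO-impregnated catheters, according to physician discretion", with no seriousness threshold. It then asks that a patient whose treatment is stopped for any reason complete all study assessments, including follow-up.

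**Recording.** 8.6 refers to section 7.5 for the criteria, requires the reason on the CRF, and sets out what to do "If a patient is withdrawn because of an AE": complete the withdrawal section and the AE module, and inform the sponsor. 16.1 adds: "The reason for premature termination must be recorded by the investigator for each patient".

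**The concern.** The primary numerators depend on one judgement per patient: did he leave the study, and was it because of an AE? The sections that guide this judgement do not match the endpoints. The withdrawal list covers only the serious part of what 5.1 counts, and a patient who leaves over a non-serious catheter complaint could be described under several of its other headings. A patient whose catheter is taken out for such a complaint may never be counted as leaving the study at all.

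The trial is open-label (6.1), its hypothesis is that the catheter is safe and tolerable (3.2), and its stated purpose is a descriptive safety and tolerability profile (7.1). Every case missed in this way lowers the proportion and so favours the hypothesis. The reason for an exit is fixed at the site when the CRF page is completed, and a later analysis plan cannot recover a cause that was never recorded.

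**Working it through.** The plan states no expected discontinuation rate, so there is no figure to reproduce. The check is a comparison of sections, followed by the size of one missed case.

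**Step 1. Which events each section covers**

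| Section | Event | Non-serious AE covered? |
|---|---|---|
| 5.1 safety | Study discontinuation, AE or SAE | Yes |
| 5.1 tolerability | Study discontinuation, catheter-associated AE or SAE | Yes |
| 13 and 13.4 | Discontinuation or non-completion due to AE | Yes |
| 8.6 | Withdrawal because of an AE | Yes, but refers to 7.5 for criteria |
| 7.5.1 | Treatment stop for suspected related AE | Yes, but patient stays in the study |
| 7.5.2 | Study withdrawal | No, serious AE only |

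Section 12 points the same way as 5.1: an abnormal test result becomes an AE if it leads the investigator to withdraw the patient, and that event need not be serious.

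**Step 2. Two routes by which a case may be missed**

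- *Route A, study exit.* A patient with a non-serious catheter complaint decides to leave. Under 7.5.2 this can be described as "1) Patient withdrew consent", as non-compliance, as failure to return or, if the catheter was changed, as replacement. Serious adverse event does not fit. If the investigator uses one of those labels alone, the exit is outside both primary numerators.
- *Route B, catheter stop.* A patient's catheter is stopped under 7.5.1 for a related AE and he attends all remaining visits. Both endpoints count discontinuation of the study, so he need not enter either numerator, even with perfect reason coding. The protocol is not uniform here: 6.1 and the per-protocol definition in 13.3 tie completing the study to completing treatment, so the same patient could be classified either way.

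**Step 3. Size of one missed case**

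Inputs: n = 6 NO patients (6.1). The protocol names no interval method, so the exact Clopper-Pearson interval is an assumption.

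- Change per case: 1/6 = 16.7 percentage points.
- 0/6: lower limit 0; upper limit 1 − 0.025^(1/6) = 45.9%.
- 1/6: lower limit 1 − 0.975^(1/6) = 0.4%; the upper limit solves (1 − p)^6 + 6p(1 − p)^5 = 0.025, giving 64.1%.
- 2/6: 33.3%, interval 4.3 to 77.7%.

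**Step 4. Effect on a test**

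Two-sided Fisher exact test against 0/6 controls: p = 1.0 for 1/6 and p = 0.45 for 2/6. No conclusion about significance changes. The effect is on the descriptive estimate.

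**The case against.** The strongest reply is that 7.5.2 lists criteria for leaving and is not a set of CRF codes. The termination page is not available here, and 16.1 does not confine the investigator to the six items. 8.6 provides an explicit path for AE withdrawal. Leaving non-serious AEs out of 7.5.2 can also be read as deliberate: stop the catheter under 7.5.1 and keep the patient in follow-up. Finally, little is lost from view. All-cause discontinuation is an observational endpoint (5.2) with a planned interval, the symptom is still tabulated as an AE with action taken and relationship (13.4), and 12 patients can be inspected one by one.

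Much of this stands, and it rules out stronger readings that a reader might infer:

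- *Such a patient will be coded as having withdrawn consent.* No section says so.
- *Only SAE withdrawals can enter the primary numerator.* 8.6 contradicts this, because it recognises withdrawal for an AE without limiting it to serious ones.
- *The chance of someone leaving measures the error.* If 5%, 10% or 20% of patients left for a non-serious AE (assumed rates), 1 − (1 − p)^6 gives a 26%, 47% or 74% chance of at least one among 6. That is the chance that a case arises, not that it is misclassified.

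The mismatch itself remains. 8.6 helps only once someone has judged the exit to be AE-driven, and for criteria it refers back to a list without that category. All-cause discontinuation is not primary, captures study exits but not catheter stops with completed follow-up, and does not show why a patient left. Reading 7.5.1 as a deliberate split does not save the endpoints either, because it is what opens Route B.

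**Conclusion.** The point holds as an inconsistency between the primary endpoints and the rules that feed them. 7.5.2 is narrower than 5.1, 8.6 and section 13, its reasons overlap, and 7.5.1 separates stopping the catheter from leaving the study while 5.1 counts only the latter. Exits or catheter stops driven by non-serious AEs may be missed by the primary safety and tolerability proportions.

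One missed case among 6 NO patients turns 16.7% into 0% and lowers the exact upper limit from 64.1% to 45.9%. This rests on 6 evaluable patients and on the Clopper-Pearson method. How often it would happen cannot be estimated from the protocol. The consequence is limited to the descriptive profile, but that profile is what the trial is meant to deliver. It is worth correcting before data collection.

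**What to change.** Reconcile 5.1, 7.5.1, 7.5.2 and 8.6 as a matter of classification only, leaving every clinical stopping and withdrawal rule as it is.

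1. On the termination page of the CRF, offer adverse event (serious or non-serious) as a reason, and record all contributing reasons.
2. State in 5.1 that any premature study exit or catheter discontinuation to which an AE contributed counts as due to an AE in the primary proportions, whatever other reason also applies. The tolerability proportion takes the subset associated with the NO catheter.
3. Show the planned all-cause discontinuation proportion next to these, with catheter stops and study exits identified separately.

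The cost is one reason code, a multiple-response field and a sentence in 5.1 with a cross-reference from 7.5.2 and 8.6. The downside is that the reported AE-discontinuation rate may be higher.

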### **7.5.3 Criteria for Study Stop**

In case of death, the study will be stopped for medical re-evaluation.

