## 6. STUDY DESIGN

### 6.1 Overview and Plan

This is a Prospective, Phase I, Open-label Case Series, Single-Center study.

A total of 12 patients, over the age of 18, undergoing radical prostatectomy will be enrolled. Screening data will be reviewed to determine patients' eligibility and informed consents will be obtained.

Patients who meet all inclusion criteria and none of the exclusion criteria will be enrolled.

6 patients will be allocated to receive NO-impregnated Foley catheters (treatment) followed by 6 patients allocated to receive non-NO-impregnated Foley catheters (control).

A patient will receive catheter up to  $21 \pm 7$  days of study treatment. A patient is considered as completed the study "per protocol", once study treatment was completed: 30-45 days after catheterization.

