Inpatient hospitalization, or prolongation of existing hospitalization, mean that hospital inpatient admission and/or prolongation of hospital stay were required for treatment of AE, or that they occurred as a consequence of the event. It does not refer to pre-planned elective hospital admissions for treatment of a pre-existing condition that has not significantly worsened, or to any diagnostic procedure.

Any new SAE that occurs after the study period and is considered to be related (possibly/probably) to the study participation should be recorded and reported immediately, as requested by the Israeli Ministry of Health (MOH).

In order to satisfy regulatory requirements, any SAE, whether deemed IP-related or not, must be reported to the sponsor and to the study monitor as soon as possible after the investigator or coordinator has become aware of its occurrence. The SAE form completion and reporting must not be delayed even if all of the information is not available at the time of the initial contact.

The SAE should be submitted to the sponsor within 24 hours of becoming aware of the event. Additional information (follow-up) about any SAE unavailable at the initial reporting should be forwarded by the site to the sponsor within 24 hours of the information becoming available.

The SAE report (initial and/or follow-up) should be sent via e-mail to:

[contact]

AND faxed to fax number: [[name]]([contact])

The e-mail or the fax confirmation should be filed in the Investigator Site File.

The SAE will be reported to the regulatory authorities (CA) and EC/IRBs, according to Israeli Ministry of Health regulations (MoH form 13 or the SAE report form can be used, as requested by the IRB).

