### **20.3 Monitor/Clinical Research Associate**

The Monitor/Clinical Research Associate (CRA) is responsible for monitoring the conduct of the study at the study centers. Monitoring visits will be arranged in advance, at a mutually acceptable time, with site personnel.

Monitoring is done by Enox personnel

The Medical Monitor is responsible for periodically reviewing all safety clinical data.

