| 3   | Erection                            | A physical examination with emphasis on the genitourinary system (penis, glans, shaft, and prepuce) will be performed on a daily basis during hospitalization, on catheter removal day, on every un-scheduled visit, and 30 days after catheterization.                                                                                                                                                                                                                                                                                                                                                                                                                                                                                                                                                                          |
| 4   | Local irritation                    | 
Biocompatibility of NO-charged catheters was evaluated by several tests conducted in animals: in vivo intradermal reactivity tests, in vivo sensitization test and in vivo safety trial for NO-charged catheters (see appendix 9, 10 and 2, in investigators brochure, respectively). All tests revealed that NO-charged catheter does not trigger dermal reaction in terms of erythema and edema. However, since NO-charged catheters will be used for the first time in human during this trial we have to consider the possibility of local irritation.
 
A physical examination with emphasis on the genitourinary system (penis, glans, shaft, and prepuce) will be performed on a daily basis during hospitalization, on catheter removal day, on every un-scheduled visit, and 30 days after catheterization.
 |

Severe adverse events which are life threatening, and/or can result in prolongation of patient hospitalization, and/or persistent or significant disability, and/or death are not expected in this study.

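### Death is the only written study-stop criterion, so in this first-in-human trial no amount of non-fatal device-related toxicity requires a pause before the next NO catheter goes in

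*Protocol*

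**What the plan says.** Section 7.5.3 of the protocol, on stopping the study, consists of one sentence: "In case of death, the study will be stopped for medical re-evaluation". It names neither a cause nor an arm.

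The other safety provisions are these:

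- **Section 7.5.1** ends catheter treatment for a single patient. One ground is "AEs that are suspected to be related to NO-impregnated catheters, according to physician discretion"; the other is a 20% limit on blood pressure and heart rate.
- **Section 7.5.2** allows, but does not oblige, a patient to be withdrawn after an SAE.
- **Section 8.6** states: "Treatment/study can be either temporarily or permanently discontinued". For the criteria it refers back to section 7.5.
- **Section 12** sets a reporting duty: "The SAE should be submitted to the sponsor within 24 hours of becoming aware of the event". Reports then go to the authorities and the ethics committee.
- **Section 20.3** states: "The Medical Monitor is responsible for periodically reviewing all safety clinical data". It gives no interval and no threshold.

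Section 6.1 has six patients receive the NO catheter first, followed by six controls. It states no sentinel patient and no spacing between insertions. Appendix 5 confirms that "NO-charged catheters will be used for the first time in human during this trial".

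**The concern.** Safety and tolerability are the primary objective, and human experience with the device starts with the first patient. The animal safety trial in section 3.1 had five rabbits with the NO catheter for 7 days, whereas a patient may carry it for up to 21±7 days.

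The toxicities that section 11.4.2 and Appendix 5 anticipate are bleeding, a fall in blood pressure, erection and local irritation. Appendix 5 does not expect life-threatening events or death. The sole stopping criterion therefore rests on an event the sponsor does not expect and is silent on the harms it does foresee. A surgical death in a control patient would stop the study, while related non-fatal SAEs in all six NO patients would not.

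Because the NO patients come first, a pause would protect exactly those still due to receive the device. Stopping criteria belong in the protocol, and this protocol has a section for them, so the point is not one left to a statistical analysis plan.

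**Working it through.** **Step 1: what each provision requires after a related, non-fatal SAE in an NO patient.**

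| Provision | Acts on | Mandatory hold on the next NO insertion? |
|---|---|---|
| 7.5.1 | that patient's catheter | No |
| 7.5.2 | that patient's participation (permissive) | No |
| 7.5.3 | the study, on death only | No |
| 8.6 | patient or study (permissive, criteria from 7.5) | No |
| 12 and 14.3, SAE reporting | information to sponsor, authorities and IRB | No |
| 20.3, Medical Monitor | periodic review, no trigger | No |

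With no deaths, the probability of a required pause is therefore 0 whatever the toxicity rate, even with six of six NO patients affected. This follows from the text and needs no assumed rate.

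**Step 2: what a non-fatal trigger would add.** The protocol gives no toxicity rate and no operating characteristic for its rule, so there is no figure to reproduce. The rates below are assumptions. Let *p* be the chance that an NO patient has an event that counts. Assume patients are independent, there are no deaths, and each outcome is known before the next insertion. A pause is in time for at least the sixth NO patient if *k* or more of the first five have an event, with X ~ Binomial(5, *p*):

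- first-event trigger (*k* = 1): 1 − (1 − *p*)^5
- second-event trigger (*k* = 2): 1 − (1 − *p*)^5 − 5*p*(1 − *p*)^4

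At *p* = 30%: 1 − 0.168 = 0.832 for the first, and 0.832 − 0.360 = 0.472 for the second.

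**Step 3: overlapping insertions.** Suppose only three outcomes are known before the sixth insertion, so X ~ Binomial(3, *p*):

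- first-event trigger: 1 − (1 − *p*)^3
- second-event trigger: 3*p*²(1 − *p*) + *p*³

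At *p* = 30%: 1 − 0.343 = 0.657, and 0.189 + 0.027 = 0.216.

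**Results: probability of a required pause before the sixth NO insertion**

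| Rule | *p* = 5% | 10% | 20% | 30% |
|---|---|---|---|---|
| Current rule, no deaths | 0% | 0% | 0% | 0% |
| First event, five outcomes known | 23% | 41% | 67% | 83% |
| Second event, five outcomes known | 2% | 8% | 26% | 47% |
| First event, three outcomes known | 14% | 27% | 49% | 66% |
| Second event, three outcomes known | 0.7% | 2.8% | 10% | 22% |

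**Step 4: a composite trigger.** Take a hold at the first related SAE or the second 7.5.1 discontinuation for suspected NO effects, and let *p* be the chance of either event in a patient. Two affected patients always fire this rule: either one of them has a related SAE, or both are discontinuations. No affected patient never fires it. Its probability therefore lies between the second-event and first-event rows: 2% to 23% at *p* = 5%, and 47% to 83% at *p* = 30%, with five outcomes known.

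**The case against.** The strongest reply is that safety oversight exists and a halt is available. Every AE gets a causality assessment. SAEs reach the sponsor within 24 hours and then the authorities and the IRB, and the Medical Monitor reviews all safety data. Section 8.6 can be read as letting any ground in section 7.5 support a study pause. Inpatients are examined daily with vital signs every 8 hours, the base catheter is an approved product, and only six patients receive NO. This is correct, and it narrows the gap to discretionary versus required. It does not close it: none of these provisions sets a threshold or ties review to the next insertion.

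Three further objections concern the size of the benefit and the choice of trigger.

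- **Timeline.** The synopsis allows about 6 months in all, with 30 to 45 days per patient. Waiting for five complete follow-ups would take 5 × 30 = 150 to 5 × 45 = 225 days before the sixth NO insertion. Overlap is therefore likely, and the three-outcome rows are a fairer guide than the five-outcome rows if full follow-up is awaited.
- **Surgical confounding.** Catheters go in on the day of prostatectomy, and bleeding and hypotension are listed NO effects. Under section 12, two of three criteria suffice for a possible relation, so an operative complication could set off a hold. This stands as a reason to choose the trigger with care.
- **Assumed rates.** Every non-zero figure depends on an assumed *p*. That also stands; only the zero is free of assumption.

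**Conclusion.** The point holds. Death is the only event that obliges anyone to stop, and no number of related non-fatal SAEs or suspected-NO discontinuations requires a pause before the next NO catheter. The probability of a required pause without a death is 0% at every toxicity rate.

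The gain from a trigger is illustrative. At an assumed 30% rate it is 47% to 83% if each outcome is known before the next insertion, and 22% to 66% if only three are, depending on whether the second or first event counts. At low rates the gain is small.

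A discretionary halt remains possible, and individual patients are protected, so this is a weakness in a stated rule and not an absence of oversight. Given first use in humans and the cheapness of the remedy, it should be corrected before the first insertion.

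**What to change.** Keep the stop for any death. Add to section 7.5.3 that NO insertions are held, pending Medical Monitor review, once a small fixed number of NO patients have either an SAE judged possibly or probably related to the catheter or a 7.5.1 discontinuation for suspected NO effects. One workable choice is the first related SAE or the second such discontinuation, with the sponsor confirming the count. Add to section 20.3 that the Medical Monitor completes this review before the next NO insertion. A stated minimum interval between the first NO insertions would keep the trigger useful, since overlap weakens it.

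The cost is one or two sentences in 7.5.3 and one in 20.3. The change relies on the existing causality scale, SAE report and Medical Monitor. The trial is open-label, so counting events unblinds nobody.

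The downside is a possible short hold on enrolment. At an assumed 5% rate its chance before the sixth NO insertion is 23% with a first-event trigger and 2% with a second-event trigger, and it rises with *p* as in the table. Operative complications classed as possibly related would add to it. If that is a worry, the SAE count can be set at two, at the price of a later warning.
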